#### Method Monitoring

There was no data monitoring board. The study team had complied with data collection and management procedures approved by the National University of Singapore ethics committee (NUS-IRB-2023‐191) and abided by the rules of medical confidentiality. We recognized the importance of safety monitoring in community-based interventions involving older adults. Accordingly, safety precautions and procedures were implemented in line with the university’s ethics committee. Trainers were briefed on these safety procedures, and, during sessions, they consistently reminded participants to exercise caution and check for potential tripping hazards while engaging in activities. Additionally, weekly post-intervention debriefings with trainers were conducted to identify any safety concerns or adverse events related to the outdoor farming sessions (Supplementary 2 in Multimedia Appendix 1). No adverse events were reported throughout the intervention, suggesting that it was conducted safely and with appropriate precautions in place. There was no independent audit of the trial.

To ensure consistency in intervention delivery, all trainers were provided with a structured facilitator manual that outlined session-by-session objectives, activities, and key content to be delivered. Teaching presentation slides were also shared with all trainers. Additionally, training sessions were conducted prior to the start of the intervention to align all trainers on core delivery principles, safety protocols, and communication style. To ensure fidelity, staff completed checklists after each session to document adherence to the protocol and note any deviations. Additionally, a member of the research team attended a random sample of sessions for verification purposes. Weekly debriefing meetings were conducted among the research team and trainers to determine whether the intervention was executed as planned, create feedback loops, and allow the early identification of problems and problem-solving to enhance implementation. We have included this fidelity assessment document in Supplementary 3 in Multimedia Appendix 1.

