## Methods

### Study Design

This UCF intervention was a parallel group, 2-arm, pragmatic waitlist randomized trial with 1:1 allocation ratio to either intervention or waitlist control. The intervention group completed the first 24-week UCF program, followed by a 24-week observation period. The control arm served as a waitlist group, receiving no intervention during the initial 24 weeks but undergoing the same intervention in the following 24 weeks after the intervention group completed. Participants in both arms completed assessment at baseline, 6-month, and 12-month follow-up. We reported using the standard protocol items: recommendation for interventional trials (Standard Protocol Items: Recommendations for Interventional Trials [SPIRIT]) checklist (Checklist 1) [29].

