15 sessions	Participants engaged in indoor plant- and farming or gardening-related knowledge-sharing sessions led by trained horticulturist farmers. Participants learned basic skills and knowledge in maintaining a garden and acquired skills in pruning, soil mixing, transplanting, and composting, as well as knowledge of the properties of plants and vegetables. Example topics included composting, the properties and nutritional value of plants and vegetables, and gardening techniques. A few indoor sessions also included microgreen planting, which participants brought home to tend to, as well as nature-art activities designed to foster creative expression and social interaction. Following the indoor activities, participants attended outdoor hands-on sessions where they engaged in green maintenance in the designated garden or farm area and practiced the gardening techniques introduced during the indoor sessions. Several outdoor sessions included therapeutic walks, during which participants took part in guided educational strolls through therapeutic gardens to learn about the unique properties of local plants and to strengthen their connection with nature. During these walks, participants engaged in sensory-based activities involving touch, scent, and visual observation, which created opportunities to reconnect with local flora and fauna and to reminisce. Several of the 15 sessions at the national garden focused on nutrition, cooking, and consumption of herbs, vegetables, and fruits. Participants learned about the nutritional value and importance of consuming more plant-based diets. Live cooking demonstrations were provided, and participants sampled the cooked vegetables. Participants were encouraged to share their recipes to promote greater social interaction.	Indoor and outdoor activities: 20 minutes of briefing of daily activities 60 minutes of indoor gardening and sharing of farming tips 60 minutes of outdoor gardening activities with short breaks in between 10 minutes of debriefing Nutrition and cooking activities: 20 minutes of briefing of daily activities 50 minutes of gardening, harvesting, and preparation 60 minutes of cooking and demonstration, food sharing, and social interaction 20 minutes of debriefing	Increase physical activity Improve gross and fine motor skills Strengthen working memory Gain a sense of achievement Care for plants—promote sense of purpose, meaningfulness, and hope Improve nutrition knowledge and attitude toward vegetable consumption Improve interpersonal interaction

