### Economic Evaluation

A cost-utility analysis will be conducted from the provider and societal perspective to assess the potential value of scaling up the UCF intervention, using QALYs as the primary effectiveness metric. This economic evaluation will be exploratory in nature and designed to inform future trial design and policy translation.

Resource use associated with the UCF intervention will be systematically recorded, including staff time (trainers), materials (gardening supplies), venue rental, and transportation. Unit costs will be derived from internal budget records and prevailing trainers’ wage rates. Any health care utilization during the intervention period (eg, GP visits, hospitalizations) will be tracked using participant self-reports and costed using standard unit prices obtained from publicly available Ministry of Health fee benchmarks or institutional databases.

Effectiveness will be expressed in terms of QALYs, derived from utility scores measured using the EQ-5D-5L instrument at baseline and postintervention. Area under the curve methods will be applied to calculate QALYs over the 24-week period. The decision tree model will be developed using the TreeAge software to compare the two scenarios: (1) the waitlist control group and (2) the urban care farming program. An incremental cost-effectiveness ratio (ICER) will be calculated as the ratio of the change in cost over QALY. The outputs of these analyses will be costs, QALY, and the incremental cost-effectiveness ratio to reflect the program’s cost-effectiveness. As Singapore does not have an official willingness-to-pay threshold for QALYs, a cost-effectiveness acceptability curve will also be plotted to show the probability that the intervention is cost-effective at varying willingness-to-pay thresholds.

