Nevertheless, this study has several limitations. The effect size used for sample size estimation was based on a prior WHOQOL study, which may not fully reflect the characteristics of the Singaporean older population or the unique aspects of the UCF intervention. The calculated sample size also includes a 20% buffer to account for expected attrition in long-term community interventions. Sensitivity analyses for secondary outcomes were not included. One methodological challenge is estimating the effect sizes of repeated measures data. To address this, the study will employ linear mixed-effects models and robust standard errors to derive reliable difference-in-difference estimates. This statistical approach enables the evaluation of longitudinal data, accounting for within-subject correlation and heterogeneity in responses over time. Attrition over the 24-week period may limit the ability to evaluate longer-term outcomes, though mitigation strategies such as regular participant engagement and reminders have been implemented. Next, the use of self-reported measures may introduce recall and reporting bias; however, the inclusion of biomarkers and clinical assessments partially mitigates this. Finally, the findings may be less generalizable to more frail or homebound populations, as the study sample consists of relatively healthy, community-dwelling individuals who are able to travel and commit to a 24-week intervention. As such, the study sample is likely skewed toward relatively healthy and motivated individuals, which may limit the generalizability of our findings. While the results offer important insights into the potential benefits of urban care farming, future work should explore adaptations of the intervention to accommodate more vulnerable older adults and assess its effectiveness in those populations. For future trials, we also recommend a more structured approach to adverse event monitoring, including standardized incident reporting forms and real-time logs, to further strengthen safety assurance and protocol reproducibility.

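### A zero count from trainer debriefings about outdoor sessions does not support the inference that the intervention was conducted safely

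*Protocol article*

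**What the plan says.** The Method Monitoring section of the protocol article describes how safety information was gathered: "weekly post-intervention debriefings with trainers were conducted to identify any safety concerns or adverse events related to the outdoor farming sessions". It cites Supplementary 2 for this, which is not shown. The next sentence draws the inference: "No adverse events were reported throughout the intervention, suggesting that it was conducted safely and with appropriate precautions in place". The same section says that there was no data monitoring board and no independent audit.

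The Discussion, among its limitations, adds for future trials: "we also recommend a more structured approach to adverse event monitoring, including standardized incident reporting forms and real-time logs".

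A second, participant-level source of health events appears in the Economic Evaluation section: "Any health care utilization during the intervention period (eg, GP visits, hospitalizations) will be tracked using participant self-reports and costed using standard unit prices". That evaluation compares the waitlist control with the farming programme. The article gives these data no safety use.

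**The concern.** A count of zero says as much about how events were sought as about how often they happened. Here the reporters are the people delivering the programme, the stated subject is outdoor sessions, and no comparator count is described. A strain or fall that becomes apparent at home, or an event in an indoor or cooking session, reaches the record only if it happens to be mentioned.

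What is at stake is the trial's safety message. Participants are aged 50 to 85, and the abstract and conclusion present the programme as a possible model for scalable community use. A reader planning such a programme could take the sentence as a trial result on safety. The Discussion recognises that monitoring should be more structured, but the inference in Method Monitoring carries no matching caveat.

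**Working it through.** A reported count of zero cannot be re-derived from other inputs, so the check has two parts: what the described route covers, and what a zero can exclude.

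**Coverage of the described route**

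| Aspect | What the article describes | What falls outside |
|---|---|---|
| Reporter | Trainers, weekly | Direct questions to participants |
| Setting | "identify any safety concerns or adverse events related to the outdoor farming sessions" | Indoor, cooking and event time |
| Comparator | Waitlist arm "receiving no intervention during the initial 24 weeks but undergoing the same intervention in the following 24 weeks" | Concurrent control events, since that arm had no trainer contact in the first 24 weeks |

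On setting, Table 1 lists 24 sessions (15 + 8 + 1). The 15 sessions at the national garden follow one of two formats:
- indoor and outdoor: 20 + 60 + 60 + 10 = 150 minutes, including "60 minutes of indoor gardening and sharing of farming tips";
- nutrition and cooking: 20 + 50 + 60 + 20 = 150 minutes, including a 60-minute cooking block.

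The single community event is a 150-minute indoor session. So 16 of the 24 sessions contain an indoor or cooking block, or are wholly indoor.

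**What zero can exclude**

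Inputs: 0 events (Method Monitoring); 67 randomised to intervention and 70 to control, 137 in total (Results). N = 137 supposes that the zero covers both delivery periods and that everyone took part.

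One-sided 95% upper limit for the per-person risk with complete capture: U = 1 − 0.05^(1/N).
- N = 67: 1 − 0.05^(1/67) = 0.0437, or 4.4%.
- N = 137: 1 − 0.05^(1/137) = 0.0216, or 2.2%.

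The upper ends of two-sided 95% intervals, 1 − 0.025^(1/N), are 5.4% and 2.7%.

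If only a share s of affected participants is captured, the limit becomes U/s. The documents give no capture rate, so s is an assumption shown over a range.

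| Assumed s | N = 67 | N = 137 |
|---|---|---|
| 1.00 | 4.4% | 2.2% |
| 0.75 | 5.8% | 2.9% |
| 0.50 | 8.7% | 4.3% |
| 0.25 | 17.5% | 8.7% |

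The chance of seeing zero when the true risk is p is (1 − p·s)^N. For an illustrative p = 5% and N = 67:
- s = 1: 0.95^67 = 0.03
- s = 0.50: 0.975^67 = 0.18
- s = 0.25: 0.9875^67 = 0.43

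With full capture, a zero would argue against a 5% risk. With partial capture it hardly does.

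**The case against.** The strongest reply has four parts.

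- **The wording is tentative and its basis is disclosed.** The article says that the zero suggests safety, and it names the debriefings in the sentence before. The debriefings were scheduled and meant to elicit events, so the zero was not merely passive. This is fair. Still, the suggestion goes beyond the source, and disclosing a narrow source does not widen it.
- **More may exist than is shown.** Supplementary 2 and the ethics-approved safety procedures are not available. Staff checklists after each session, sampled attendance by a research team member and weekly team meetings are also described, and these are not limited to outdoor time. Trainers saw participants weekly, so later problems could surface. The phrase about outdoor sessions may also be loose shorthand for the whole programme. These points stand as reasons to check Supplementary 2 before rewording. The checklists and sampled visits, however, are described as fidelity tools.
- **The weakness is acknowledged.** It is, but only as advice for future trials.
- **Efficacy is untouched.** True: randomisation, sample size and the primary analysis are unaffected.

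A reader might be tempted to infer three stronger things that the documents do not support.

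1. *The zero is implausible given the exposure.* Calendar exposure is 137 × 24/52 = 63.2 person-years. But session time is 24 × 2.5 to 3 hours = 60 to 72 hours each, or 8,220 to 9,864 hours for 137 people. At 8,766 hours per year that is about 0.9 to 1.1 person-years, even with full attendance. No background event rate is given, so the zero cannot be called implausible.
2. *Only one arm was ever observed.* Both arms received the programme in turn, so the debriefings may cover both delivery periods. What is missing is a concurrent control count.
3. *Two-arm health-care-use data are certainly in hand.* The cost comparison implies it, but the Economic Evaluation section does not say that both arms were asked, and Table 2 does not list health-care use.

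**Conclusion.** The point holds as an unsupported inference. The described source, trainer debriefings about outdoor sessions with no described participant-level solicitation and no concurrent waitlist capture, can support a statement about what trainers reported. It cannot support a statement that the intervention was conducted safely.

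At best, zero events exclude per-person risks above 4.4% (67 participants) or 2.2% (137 participants), one-sided 95%, and only if capture was complete. Under assumed capture of 25% to 75%, the limits run from 5.8% to 17.5% for 67 and from 2.9% to 8.7% for 137.

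The conclusion rests on the article's own description of its route and would soften if Supplementary 2 shows wider capture. A reader might infer that the programme was unsafe or that events were missed; nothing in the article shows either. The primary efficacy conclusion is not affected, but what the trial can say about safety is.

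**What to change.** 1. Replace the inference in Method Monitoring with a statement of what was observed, for example: *trainers reported no adverse events related to outdoor sessions at weekly debriefings; events outside sessions and in the waitlist arm were not systematically sought*. Check this against Supplementary 2 first, and align it with the limitation in the Discussion.
2. If an upper limit is added (4.4% for 0/67 or 2.2% for 0/137, one-sided 95%), label it a best case that assumes complete capture.
3. Report self-reported GP visits and hospitalizations by randomised arm from baseline to 6 months as a descriptive safety comparison, after confirming that both arms were asked. If they were not, say so and omit the table.
4. Add health-related withdrawals or session absences only if reasons were recorded. The article allows withdrawal without giving a reason and describes attendance sheets only for monitoring adherence.

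The cost is small: one reworded sentence and, if the data exist, one table. Data collection is complete, so fields that were not collected prospectively cannot be supplied now, but analysis of the 6-month data is still under way. The downsides are a less favourable safety statement and the fact that self-reported health-care use is a coarse proxy for harm.

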### Economic Evaluation

A cost-utility analysis will be conducted from the provider and societal perspective to assess the potential value of scaling up the UCF intervention, using QALYs as the primary effectiveness metric. This economic evaluation will be exploratory in nature and designed to inform future trial design and policy translation.

Resource use associated with the UCF intervention will be systematically recorded, including staff time (trainers), materials (gardening supplies), venue rental, and transportation. Unit costs will be derived from internal budget records and prevailing trainers’ wage rates. Any health care utilization during the intervention period (eg, GP visits, hospitalizations) will be tracked using participant self-reports and costed using standard unit prices obtained from publicly available Ministry of Health fee benchmarks or institutional databases.

Effectiveness will be expressed in terms of QALYs, derived from utility scores measured using the EQ-5D-5L instrument at baseline and postintervention. Area under the curve methods will be applied to calculate QALYs over the 24-week period. The decision tree model will be developed using the TreeAge software to compare the two scenarios: (1) the waitlist control group and (2) the urban care farming program. An incremental cost-effectiveness ratio (ICER) will be calculated as the ratio of the change in cost over QALY. The outputs of these analyses will be costs, QALY, and the incremental cost-effectiveness ratio to reflect the program’s cost-effectiveness. As Singapore does not have an official willingness-to-pay threshold for QALYs, a cost-effectiveness acceptability curve will also be plotted to show the probability that the intervention is cost-effective at varying willingness-to-pay thresholds.

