### Ethical Considerations

The study has been approved by the National University of Singapore Institutional Review Board (NUS-IRB-2023‐191). The approval has also been granted for the pilot study of this project. Any modification to the approved protocol will be submitted for review by the ethics committee. If there are any amendments, changes will be reflected in the trial registry. All participants provided written consent prior to the participation. Data collected was anonymized and kept confidential. Consent from participants was obtained to publish the results from deidentified data. To acknowledge the time and effort required, participants were provided with a S$30 (US $22.05) [30] honorarium for each data collection session (approximately 210 min). The amount was set at a level appropriate to compensate participants without constituting undue inducement, consistent with ethical guidelines for research involving human participants. Participants’ data (eg, case record forms, laboratory tests, information sheets, and consents) are stored in a locked cabinet in a researcher’s office. All other data (eg, biomarker results, and responses to surveys) have been deidentified. All personal identifier data (eg, names and contact information) are kept separate from the research data by a trusted third party. All data collection has been completed, and a link (otherwise known as code key) was passed to the trusted third party so the research team only works with deidentified data. After the study has been completed, all personal data will be kept for a maximum of 5 years. Research and biological data will be kept for a maximum of 10 years. During the study, the data will only be accessible to the research team. The research team has exclusive rights to the deidentified data for 36 months after the trial is completed.

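### QALYs come from a two-point area under the curve with no stated adjustment for baseline utility, and the named costs do not support the societal perspective

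*Protocol article*

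**What the plan says.** The Economic Evaluation section states: "A cost-utility analysis will be conducted from the provider and societal perspective". Effectiveness is expressed in QALYs, "derived from utility scores measured using the EQ-5D-5L instrument at baseline and postintervention", and "Area under the curve methods will be applied to calculate QALYs over the 24-week period". A decision tree compares the two scenarios, then "An incremental cost-effectiveness ratio (ICER) will be calculated as the ratio of the change in cost over QALY", and an acceptability curve follows. No adjustment for baseline utility is mentioned.

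The Statistical Analysis section does plan adjustment or matching on baseline covariates, but ties it to the difference-in-difference analysis. The covariates given as examples are demographic, and utility is not among them. EQ-5D-5L appears in Table 2 but is not described under Secondary Outcomes.

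On costs, the programme resources are listed as "including staff time (trainers), materials (gardening supplies), venue rental, and transportation", with unit costs from internal budgets and trainers' pay rates. Health care use "will be tracked using participant self-reports" and is priced from fee benchmarks or institutional databases. The UCF Intervention section states that participants were reimbursed S$10 per session for travel. The Ethical Considerations section states: "All data collection has been completed".

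**The concern.** With only two utility measurements, the baseline value makes up half the weight of each person's area under the curve. Any difference between arms at baseline precedes the intervention, yet it passes straight into the QALY difference unless the comparison adjusts for it. Over 24 weeks the attainable QALY gain is small, so an ordinary chance imbalance could change the size or even the sign of the ICER. The primary analysis avoids this through its group-by-time interaction; the QALY analysis as described has no such protection.

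Two lesser matters sit in the same section. A reader will take a societal result to count what participants and carers give up, and no such item is named. Health care use is described as still to be collected in a trial whose data collection is finished, so it is unclear whether that cost component exists in both arms.

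**Working it through.** The economic section gives no figure to reproduce. The trial's sample size was set on the WHOQOL score and does not speak to QALY precision.

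**Inputs from the article:** 24-week horizon; utilities at two points; 67 and 70 randomized; 24 weekly sessions of 2.5 to 3 hours.

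**Assumptions, because the documents give none:** utility SD 0.10 to 0.20, equal at both times; true utility gain at 24 weeks 0.02 to 0.05; correlation between the two utilities (rho) 0.5 or 0.7.

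**Step 1, weight of the baseline difference.** QALY = (24/52) x (u0 + u1)/2. With d0 and d1 the between-arm differences at baseline and follow-up, the QALY difference is 0.2308 x (d0 + d1), since 0.5 x 24/52 = 0.2308. Each 0.01 of baseline difference adds 0.0023 QALY directly.

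**Step 2, size of a chance imbalance.** SE(d0) = SD x sqrt(1/67 + 1/70) = SD x 0.1709.

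| Assumed SD | SE(d0) | Direct QALY shift, 0.2308 x SE(d0) |
|---|---|---|
| 0.10 | 0.0171 | 0.0039 |
| 0.15 | 0.0256 | 0.0059 |
| 0.20 | 0.0342 | 0.0079 |

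With 57 per arm, the number before the dropout allowance, the range is 0.0043 to 0.0086.

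**Step 3, size of the signal.** A true gain g is worth 0.2308 x g: 0.0046, 0.0069 and 0.0115 QALY for g = 0.02, 0.03 and 0.05. The direct shift from one SE is therefore between 0.34 (0.0171/0.05) and 1.7 (0.0342/0.02) times the signal.

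**Step 4, carry-over.** Baseline imbalance also shifts expected follow-up utility by rho x d0, so the full shift is 0.2308 x (1 + rho) x d0. With SD 0.15, rho 0.5 and g = 0.03, one SE gives 0.2308 x 1.5 x 0.0256 = 0.0089. For an illustrative incremental cost of 1,000 currency units:

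| Baseline difference | Expected unadjusted QALY difference | Cost per QALY |
|---|---|---|
| -1 SE | 0.0069 - 0.0089 = -0.0019 (from unrounded values) | dominated |
| 0 | 0.0069 | about 144,000 |
| +1 SE | 0.0069 + 0.0089 = 0.0158 | about 63,000 |

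Adjusted for baseline utility, the expected difference is 0.0069 (about 144,000 per QALY) in all three rows.

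**Step 5, precision.** The variance of u0 + u1 is 2 x SD^2 x (1 + rho). Given u0, it is SD^2 x (1 - rho^2). The ratio is 2/(1 - rho): 4.0 at rho 0.5 and 6.7 at rho 0.7. At SD 0.15 the SE of the QALY difference falls from 0.0102 to 0.0051 (rho 0.5), or from 0.0109 to 0.0042 (rho 0.7).

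**Step 6, costs.** The named items are trainer time, materials, venue, transportation and health care use. Participant time, lost productivity and informal care are absent, and none of the stated unit-cost sources would value them. Transportation may be a participant cost, but the study reimbursed travel. Full attendance takes 24 x 2.5 = 60 to 24 x 3 = 72 hours per participant, or 67 x 60 = 4,020 to 67 x 72 = 4,824 hours across the intervention arm.

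**The case against.** The strongest reply is that the article does not say the comparison is unadjusted. Area under the curve describes how each person's QALYs are built, not how arms are then compared, and the remedy leaves that sentence intact. An article may leave the covariate to a fuller health-economic plan, and the Introduction calls these evaluations subsequent and separate. This stands: a reader might infer that the plan fixes an unadjusted analysis, but it is only silent. What remains is that the text, followed as written, gives no protection, and that the one passage on baseline adjustment points elsewhere.

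A reader might also infer that half of the QALY difference is the baseline difference, or that the ICER is biased. Neither follows. The baseline term has half the weight, but its share depends on the data: with SD 0.15, gain 0.05, rho 0.6 and d0 at +1 SE, d1 = 0.05 + 0.6 x 0.0256 = 0.0654, and the share is 0.0256/0.0910, about 28%. Under randomization its expectation is zero. A properly built acceptability curve would reflect the extra uncertainty, though it would be wider than necessary.

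On costs, the resource list is open-ended, and leaving out productivity or informal care could omit savings as well as losses, so it is not shown that cost is understated. A plain provider label would not fit either, because GP visits and hospital stays are not costs of the farming provider.

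On health care use, Table 2 has no such item, but it is not a full inventory: housing type and serum creatinine are named elsewhere in the article and are missing from it too. The future tense may be a slip, since programme resources are also described as yet to be recorded. It cannot be concluded that the data were never collected.

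Finally, the section says: "This economic evaluation will be exploratory in nature and designed to inform future trial design and policy translation". That limits the severity, although policy translation is one of its stated aims.

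**Conclusion.** The point holds as an improvement of low severity, not as a stated error. A two-point area under the curve with no stated baseline adjustment lets chance imbalance into the QALY difference with weight 0.23, plus carry-over. Under the assumed SDs of 0.10 to 0.20, one standard error of imbalance adds 0.0039 to 0.0079 QALY directly, against 0.0046 to 0.0115 QALY for assumed gains of 0.02 to 0.05. This is lost precision, and in this trial's single ICER it could change the size or sign. The sizes rest on assumed SDs, gains and correlations; the weight and the variance ratio 2/(1 - rho) follow from the two-point formula, the ratio also from equal variances at the two times.

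The societal label goes beyond the costs named. The status of the health care data needs a plain statement. None of this touches the primary outcome.

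**What to change.** 1. State that incremental QALYs will be estimated by regressing individual area-under-the-curve QALYs on allocation and baseline EQ-5D-5L utility. Use those adjusted QALYs, bootstrapped jointly with costs, for the ICER and acceptability curve.
2. Either add participant time (attendance sheets x session length x a stated wage rate) and name the societal items still excluded, such as productivity and informal care, or relabel the perspective as provider plus health care.
3. Reconcile the planned tracking of health care use with completed data collection: state whether it was collected, how and in which arms. Include it in costs only if it was collected in both.

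The cost is small: one covariate already held, attendance records already kept and a few sentences. The article reports that analysis of the baseline and 6-month data is still under way, so the change can be fixed beforehand if the economic results have not been examined. The price is a narrower claim of perspective or a different cost total.
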